### **Hypothetical Mechanism and Conventional Treatment of Long COVID**

There is no universally established definition for what is commonly referred to as Long COVID, with different countries and institutions using varying terms and definitions. The World Health Organization (WHO) defines Post-COVID Conditions as symptoms that cannot be explained by an alternative diagnosis, occurring within three months of COVID-19 symptom onset and lasting for at least two months[6]. The U.S. Centers for Disease Control and Prevention (CDC) defines Post-COVID Conditions (Long COVID) as symptoms persisting for more than four weeks after the initial infection. The National Institute for Health and Care Excellence (NICE) in the UK defines Ongoing symptomatic COVID-19 as symptoms lasting 4-12 weeks, and Post-COVID syndrome as symptoms persisting beyond 12 weeks and not explained by other diagnoses[7].

In South Korea, there is a need to unify terminology for research and case definitions related to post-COVID-19 sequelae. Through discussions between the Korea Disease Control and Prevention Agency (KDCA) and the Korean Society of Infectious Diseases, Long COVID has been defined as symptoms or signs lasting beyond 12 weeks after COVID-19 diagnosis that cannot be explained by other diseases. Acute or subacute complications of COVID-19, such as venous thromboembolism, myocarditis, pericarditis, encephalitis, and thyroiditis, are not classified as Long COVID. The symptoms commonly associated with Long COVID include fatigue, shortness of breath, depression, anxiety, and cognitive decline[8].

## **Fatigue**

Fatigue is one of the common non-respiratory symptoms experienced by COVID-19 patients, with approximately 41% reporting it. It is reported to occur in 35-45% of patients at four weeks, 30-77% at eight weeks, and 16-55% at twelve weeks post-infection. The fatigue experienced by COVID-19 patients resembles chronic fatigue syndrome (CFS) described after

Middle East respiratory syndrome (MERS), severe acute respiratory syndrome (SARS), or community-acquired pneumonia. However, there has been no reported correlation between the severity of COVID-19 and long-term fatigue symptoms or related laboratory inflammatory markers. Excessive fatigue has been noted in female patients previously diagnosed with depression or anxiety. The fatigue associated with Long COVID can be more extensive and severe, including symptoms such as sore throat, generalized pain, changes in blood pressure, gastrointestinal issues like irritable bowel syndrome, headaches, sleep disturbances, depression, and dizziness. More severe neurological symptoms such as new sensitivities or allergies, burning or tingling sensations in the limbs, may also occur. A key characteristic of this condition is the sudden worsening of symptoms with minimal physical or mental activity. Since these symptoms align with chronic fatigue syndrome (also known as myalgic encephalomyelitis or ME), the WHO classifies these symptoms within the same category of neurological disorders. Clinical evaluations for post-viral fatigue syndrome are conducted similarly to those for chronic fatigue syndrome.

The exact mechanisms behind post-viral fatigue syndrome are not yet fully understood. Hypotheses include abnormal reactions to latent viruses in the body, increased levels of pro-inflammatory cytokines, and neuroinflammation. Specifically, the phenomenon known as a 'cytokine storm,' involving a surge of cytokines like IL-2, IL-7, granulocyte, interferon-gamma, monocyte, and TNF-alpha triggered by viruses, leading to multi-organ damage, can result in long-term functional impairment post-recovery. This may lead to disorders such as post-encephalitis syndrome, with disruptions in cytokine signaling pathways causing symptoms like fatigue. Therefore, a holistic approach is likely needed to recover immune function and improve organ function in individuals experiencing Long COVID[9]. However, there is currently

a lack of high-level evidence supporting the effectiveness of treatments and interventions for managing fatigue in Long COVID patients. As a result, symptomatic and lifestyle management remains the primary mode of treatment, highlighting an urgent need for further research in this area[8] .

### **Evidence for Kyungok-go in Treating Post-COVID-19 Sequelae**

Literature studies on chronic fatigue syndrome in traditional Korean medicine identify several patterns, including spleen qi deficiency, liver-spleen disharmony, qi deficiency with blood stasis, liver-kidney yin deficiency, and spleen-kidney yang deficiency, with spleen qi deficiency being the most common pattern[10] . A survey of Korean traditional medicine practitioners revealed that herbal medicine is the most effective and widely used treatment for chronic fatigue syndrome and idiopathic chronic fatigue, with formulas such as Bojungikgi-tang, Ssanghwa-tang, Sipjeondaebo-tang, Guipi-tang, Palmul-tang, Gongjin-dan, and Kyungok-go frequently selected for treatment[11] . Kyungok-go is clinically used to improve fatigue and related symptoms after illnesses characterized by qi and yin deficiency.

In an experimental study, ICR mice treated with 600 mg/kg of Kyungok-go for four weeks showed significant reductions in blood lactate, increased blood glucose levels, increased glycogen content in skeletal muscle, improved grip strength, enhanced treadmill exercise performance, and prolonged forced swimming exercise duration, indicating anti-fatigue effects and improved exercise performance[12] . Clinical evidence suggests that Kyungok-go is effective in reducing lactate and ammonia levels after incremental exercise, and it has been shown to increase maximal oxygen uptake and heart rate recovery after exercise, aiding in aerobic exercise capacity and post-exercise recovery in soccer players[13] [14] .

Moreover, Kyungok-go was the most prescribed herbal medicine for COVID-19 treatment in Korea during the first half of 2020, and it has been reported to improve COVID-19 related symptoms, including fatigue [15]. Studies also suggest potential applications of Kyungok-go in managing neuroinflammation and neurodegenerative diseases. In BV2 microglial cells, Kyungok-go was found to inhibit the production of NO, iNOS, COX-2, and various cytokines during inflammation [16]. Additionally, literature on Kyungok-go indicates its antioxidant, anticancer, anti-inflammatory, immune-boosting, and growth-promoting effects, making it applicable to a variety of conditions in the central nervous, cardiovascular, digestive, and respiratory systems without significant toxicity or side effects [17]. Kyungok-go is listed in the Korea Ministry of Food and Drug Safety as a herbal medicine indicated for conditions such as physical weakness and fatigue, suggesting its potential application in alleviating fatigue symptoms associated with Long COVID. Establishing clinical evidence for this application is crucial for developing traditional Korean medicine management strategies for Long COVID.

## **2) Purpose of the Study**

The purpose of this study is to conduct a prospective preliminary clinical trial to evaluate the safety and efficacy of an over-the-counter herbal medicine in individuals who experience fatigue as a symptom of Long COVID after recovering from COVID-19. The trial aims to assess the feasibility of the intervention and research design for future large-scale studies. The primary objective is to explore changes in the Fatigue Severity Scale (FSS) after 12 weeks of taking the herbal medicine (Kyungok-go) in patients with Long COVID-related fatigue. The secondary objective is to evaluate the feasibility of the study design by monitoring recruitment rates and dropout rates during the study period. Additionally, the study aims to explore the

impact of the herbal medicine on COVID-19 immune responses and metabolites associated with fatigue in post-COVID-19 patients.

## **6. Target disease**

Persistent fatigue following COVID-19 infection

## **7 . Subject selection**

### **1) Inclusion criteria**

- Adults aged 19 and above who have been diagnosed with COVID-19 for at least 12 weeks.
- Individuals who have experienced fatigue for more than 4 weeks that was not present before their COVID-19 diagnosis.
- Individuals with an FSS score of 4 or higher.
- Individuals with no significant cognitive impairments who voluntarily consent to participate in the study through written consent.

### **2) Exclusion criteria**

- Individuals with a history or current condition of diseases that can cause fatigue (e.g., cancer, sleep disorders, chronic hepatitis, liver cirrhosis, chronic renal failure, tuberculosis, asthma, multiple sclerosis).
- Individuals with conditions that can affect drug absorption or metabolism (e.g., dysphagia, clinically significant gastrointestinal disorders, galactose intolerance, Lapp lactase deficiency, glucose-galactose malabsorption).
- Uncontrolled diabetic patients.
- Individuals with a history of allergies to the investigational medicinal product (herbal medicine).
- Individuals with a history of liver or kidney diseases, or blood tests showing AST, ALT, BUN,

or creatinine levels exceeding three times the upper limit of normal.

- Pregnant or breastfeeding women, or those with the potential to become pregnant.
- Individuals who have participated in another clinical trial within 30 days prior to the study.
- Individuals who have taken herbal or herbal medicine (containing the same ingredients as the investigational medicinal product) within two weeks prior to the study.
- Individuals whom the researcher deems unable to participate in the study due to clinically significant psychiatric symptoms, medical conditions, or laboratory findings.

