|                                                    | 
 
● Liver or kidney disease history or lab results exceeding 3 times the upper normal limit for AST, ALT, BUN, Creatinine.
 
● Women who are pregnant, may become pregnant, or are breastfeeding
 
● Participation in another study within the last 30 days
 
● Clinically significant psychiatric symptoms or medical conditions as judged by the investigator
 
                                                                                                                                                                                                                                                                                                                                                                                                          |       |                                     |
| Target Number of Participants               | This pilot study aims to recruit 100 participants, with 50 in the Kyungok-go treatment group and 50 in the placebo group.                                                                                                                                                                                                                                                                                                                                                                                                                                                                                                                                                                                                                                                                                                                     |       |                                     |

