## Schedule Summary

| Visit                                                                      | 0       | One  | 2      | 3      | 4       | UV * |
|----------------------------------------------------------------------------|---------|------|--------|--------|---------|------|
| Week (day)                                                                 | -1 (-7) | 1(0) | 4 (28) | 8 (56) | 12 (84) | -    |
| Visit window (day)                                                         | -       | +2   | ±2     | ±2     | ±2      | -    |
| Written Consent                                                            | ●       |      |        |        |         |      |
| Demographic Survey                                                         | ●       |      |        |        |         |      |
| Participation in Other Clinical Trials                                     | ●       |      |        |        |         |      |
| Physical Exam                                                              | ●       |      |        |        |         |      |
| Medical History                                                            | ●       | ●    |        |        |         |      |
| COVID-19 Diagnosis                                                         | ●       |      |        |        |         |      |
| Concomitant Medication/Treatment                                           | ●       |      |        |        |         |      |
| Vital Signs                                                                | ●       | ●    | ●      | ●      | ●       | ●    |
| Electrocardiogram                                                          | ●       |      |        |        | ●       | ●    |
| Laboratory Test                                                            | ●       |      |        |        | ●       | ●    |
| Immune, Metabolite Test (Blood Collection)                                 | ●       |      |        |        | ●       | ●    |
| Pregnancy Status Evaluation **                                             | ●       |      |        |        |         |      |
| Fatigue Symptom Evaluation ***                                             | ●       |      |        |        |         |      |
| FSS (Fatigue Severity Scale)                                               | ●       |      | ●      | ●      | ●       | ●    |

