  - Blood chemistry: AST, ALT,  $\gamma$ -GTP, ALP, HbA1c (considered diabetes if abnormal), BUN, creatinine, total bilirubin, glucose.
  - Immunology: COVID-19 specific antibody/neutralizing antibody tests, single-cell transcriptome analysis (scRNA seq.) for immune-related gene expression comparison, FACS for immunophenotyping, serum cytokine levels.
  - Metabolomics: primary and secondary metabolite profiling.
- ⑩ Perform a pregnancy test (urine or serum  $\beta$ -hCG) for women of childbearing potential (test results within 28 days of screening can be used).
- ⑪ Participants follow the investigator's instructions for the following evaluations:
  - Fatigue assessment using FSS.
  - Evaluation of whether fatigue symptoms have persisted for more than four weeks.
- ⑫ Confirm inclusion/exclusion criteria.

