#### 11.4.1.2 Visit 1 ( start of intervention , Week 1)

If all tests and eligibility assessments are completed during the screening visit, Visit 1 can be conducted on the same day to assign participant numbers. If the screening visit and assignment of participant numbers occur on the same day, overlapping evaluations are performed only once.

- ① Measure vital signs.
- ② Investigate past and current medical history (changes between Visit 0 and Visit 1).
- ③ Assign random numbers.
- ④ Prescribe a four-week supply of the assigned herbal medicine based on the random number.
- ⑤ Participants follow the investigator's instructions for the following evaluations:
  - Assess fatigue severity using a 0-100 VAS.
  - Evaluate fatigue using the Chalder Fatigue Scale (ChFS).
  - Assess quality of life using EQ-5D-5L.
  - Evaluate sleep status using PSQI-K (Korean version of the Pittsburgh Sleep Quality Index).
  - Conduct cognitive function tests using K-MOCA (Korean-Montreal Cognitive Assessment).
  - Evaluate depression using Beck's Depression Inventory (BDI).

- Perform digit span tests (forward and backward).
- Conduct computerized neurocognitive function tests.
- Perform the Short Physical Performance Battery (SPPB).

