**
 Types of human specimens, analytical methods, performing institution and analysis purpose**

#### 11.4.2.12 Assessment of pregnancy and lactation

For women of childbearing age, a  $\beta$ -hCG test is performed using serum or urine tests (sticks). If there are test results within 28 days before herbal medicine administration, this test can be omitted. Women who are menopausal (at least one year of amenorrhea), have undergone a hysterectomy, or have had both ovaries (or fallopian tubes) removed are excluded from the test. The potential for pregnancy and lactation is confirmed verbally.

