**1 3. Criteria for discontinuation and withdrawal of subjects, and termination of the clinical trial**

The participation status of all subjects in this clinical trial will be recorded. If the administration of the investigational medicinal product or observation is discontinued, the reason will be documented. The conditions under which a subject may discontinue participation are as follows:

- ① In case of acute reactions (allergy, hypersensitivity, etc.) to the herbal preparation.
- ② If it is found that a subject does not meet the inclusion/exclusion criteria.

- ③ If unforeseen diseases or accidents occur making administration and observation impossible.
- ④ If "serious adverse reactions" or "severe adverse drug reactions" occur, making continued administration and observation inappropriate.
- ⑤ If the subject becomes pregnant.
- ⑥ If the subject or their proxy requests to discontinue participation (withdrawal of consent).
- ⑦ Any other reasons deemed appropriate by the researcher for discontinuing the trial.

The termination criteria for this clinical trial are as follows.

The clinical trial will be terminated when the target number of subjects is enrolled, and data integrity is ensured. The principal investigator will record the termination date and conduct data analysis once the follow-up for the last subject is completed. For individual subjects, the clinical trial will conclude upon completion of planned visits and evaluations, and the processes specified in the protocol.

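### Visit 0 item 10 counts a pregnancy test's 28-day validity from screening and Section 11.4.2.12 counts it from administration, so item 10 alone can pass a result 35 to 37 days old at first dose

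*Protocol*

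**What the plan says.** The Protocol excludes "Pregnant or breastfeeding women, or those with the potential to become pregnant" (Section 7, exclusion criteria), and the Summary excludes "Women who are pregnant, may become pregnant, or are breastfeeding". A β-hCG test supports the check, and a recent result may replace a new one. Two places say how recent it must be:

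- Section 11.4.1.1 (Visit 0), item 10, asks for a urine or serum test "for women of childbearing potential (test results within 28 days of screening can be used". The reference date is screening.
- Section 11.4.2.12 says: "If there are test results within 28 days before herbal medicine administration, this test can be omitted". The reference date is administration.

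In the Schedule Summary, the row "Pregnancy Status Evaluation" is marked at Visit 0 only, as is the check of the inclusion and exclusion criteria. Visit 0 is at Day -7. Visit 1, where treatment is assigned and dispensed, is at Day 0 with a window of +2 days. The Visit 1 list (Section 11.4.1.2) contains "Investigate past and current medical history (changes between Visit 0 and Visit 1" but no pregnancy test. The two visits may be combined: "Visit 1 can be conducted on the same day to assign participant numbers".

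**The concern.** One validity rule has two reference dates, and on the planned schedule these lie a week apart. The looser version sits in the Visit 0 list, which staff work from on the day. The stricter version sits in the later description of the assessment. A coordinator following item 10 to the letter can accept a result that Section 11.4.2.12 would not accept at first dose, and no later test would pick this up. At stake is whether a participant can start 12 weeks of dosing on a pregnancy result older than the protocol's own limit before administration.

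**Working it through.** The check is day arithmetic on the schedule. The plan states no figure for the age of the test at first dose, so there is none to reproduce.

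**Inputs**

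- Oldest result accepted under item 10: 28 days at Visit 0 (Section 11.4.1.1).
- Limit under Section 11.4.2.12: 28 days at administration.
- Gap from Visit 0 to Visit 1: 7 days nominal, 7 + 2 = 9 days at the end of the Visit 1 window (Schedule Summary), 0 days if the visits are combined (Section 11.4.1.2).
- Assumption: the first dose is taken on the day of Visit 1.

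**Formulas**

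- Age at first dose = age at Visit 0 + gap.
- Oldest age at first dose under item 10 alone = 28 + gap.
- Excess over the limit = (28 + gap) - 28 = gap.
- A reused result breaches the limit when age at Visit 0 + gap > 28, that is, when age at Visit 0 > 28 - gap.

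**Results**

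| Visit 0 to Visit 1 | Oldest at first dose, item 10 alone | Excess over 28 days | Age at Visit 0 that leads to a breach |
|---|---|---|---|
| Same day (gap 0) | 28 + 0 = 28 | 0 | none |
| Nominal (gap 7) | 28 + 7 = 35 | 7 | over 28 - 7 = 21, so 22 to 28 days |
| End of window (gap 9) | 28 + 9 = 37 | 9 | over 28 - 9 = 19, so 20 to 28 days |

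A test done at Visit 0 itself is 0, 7 or 9 days old at first dose and never comes near the limit. If both sections are applied, the stricter one governs and the maximum is 28 days in every row.

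**The case against.** The two rules can be met together. Item 10 is permissive, Section 11.4.2.12 is the dedicated pregnancy section and is stricter, and a site that reads both complies with both. A breach needs several things at once: an outside result is reused, it is already about three to four weeks old, the visits fall on different days, and staff do not consult the later section. The protocol itself tolerates a result 28 days old, and neither its product precautions (Section 12) nor its list of risks (Section 27) names a pregnancy hazard that a further 7 to 9 days would worsen. Visit 0 has no stated window, so 37 days is what the printed schedule gives and not a hard ceiling.

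All of this stands, and it keeps the severity low. It does not remove the conflict, because item 10 expressly permits a result that Section 11.4.2.12 does not.

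A reader might go further and infer that the eligibility rule itself is unsettled. Item 10 tests women of childbearing potential, and Section 13 lists "If the subject becomes pregnant" among the reasons to discontinue, as though women able to conceive could enter after a negative test. The documents do not support that. The exclusion appears twice, consistently and without qualifier. The same criterion separately bars women who are already pregnant, which is what the test detects. Section 11.4.2.12 and the schedule footnote define the tested group by childbearing age, and potential for pregnancy is settled verbally. The test and the discontinuation rule can therefore serve as back-up checks beside a full exclusion, and no text says that such women are enrolled.

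**Conclusion.** The inconsistency in the test window is real and small. Under item 10 alone, the oldest acceptable result exceeds the Section 11.4.2.12 limit by 7 days on the nominal schedule and by 9 days at the end of the Visit 1 window. There is no excess when the visits are combined or the test is done at Visit 0. This rests on reading item 10 as up to 28 days before the screening visit, on first dosing at Visit 1, and on the printed 7-day gap. How many participants would bring a reused result in the affected range cannot be known from the protocol. The documents show that item 10 allows an older result. They do not show that anyone would be dosed on one or harmed by it. The point is a low-priority correction for participant safety, with no effect on any endpoint, analysis or the planned 100 participants.

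**What to change.** Change Section 11.4.1.1 item 10 to require a negative result within 28 days before first administration, in line with Section 11.4.2.12. Add to the Visit 1 list (Section 11.4.1.2) and to the Schedule Summary a repeat urine stick test, needed only when a reused result would be more than 28 days old at first dose. Leave the exclusion criterion and the discontinuation rule as they are.

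The cost is wording in three places and an occasional extra stick test, a method that Section 11.4.2.12 already allows. No statistical figure changes.
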